### Description of the intervention: Disease Management Programme

The DMP, which will be carried out by the case manager, has three main components: education of the patient and the main caregiver to improve disease knowledge and self-management, monitoring of the patient's clinical condition, and monitoring of treatment compliance.

a) DMP components to be conducted by the case manager during the hospital stay

i- Provision of information to patients and their caregivers or family members. An individual session will be held to teach the characteristics, causes and prognosis of HF. Emphasis will be given to recognition of symptoms of decompensation, precipitating factors, and treatment (drug knowledge and treatment compliance).

ii- Provision of written and graphic educational materials with the foregoing information.

iii- Health education on warning signs and symptoms and information on drugs for the most common comorbidities: diabetes, COPD and depression.

iv- Coordination of hospital discharge with ward nursing staff

v- Development of a follow-up plan. A date for an outpatient appointment will be set, and a telephone contact number will be provided to patients so they can ask questions or report any incidents.

b) Components of the DMP to be conducted by the case manager after hospital discharge

The case manager will devote 2 days/week to the clinical assessment of outpatients. The first contact with the patient will be by telephone, in the second week after hospital discharge: during this call, the case manager will verify the patient's knowledge of HF, reinforce the information provided during hospitalisation, and strengthen compliance with recommended lifestyles and pharmacological treatment. Control of minor symptoms of decompensation by use of diuretics will be emphasized. The first visit will take place at the hospital outpatient clinic 4 weeks after discharge. Future visits will be agreed according to the patient's clinical and treatment needs, but some minimum controls will be established at months 1, 2, 3, 6, 8 and 12 after discharge (table 1). The case manager will be provided with a cell phone to facilitate coordination with patients, caregivers and other health professionals. Messages left with the case manager will be answered within 24 hours.

**Table 1 T1:** Design and data collection in the HF-Geriatrics study

TIME	CONTROL GROUP	INTERVENTION GROUP	WHO DOES IT
Admission	Review of inclusion and exclusion criteria Informed consent Randomisation **BASELINE VARIABLES**		Case manager
		
	ROUTINE MEDICAL MONITORING (will vary across centres)	Educational session Knowledge of disease Drugs Comorbidity Follow-up information Plan for discharge Questionnaires on self-care and disease knowledge for patient and caregiver	
		
2 weeks		Telephone contact Symptoms-signs Compliance Next appointment	Case manager
		
1 month		Consultation with case manager Educational reinforcement Drugs-Compliance Comorbidity Follow-up	Case manager
		
2 months		Consultation with case manager Similar to above	Case manager
		
3 months		Consultation with case manager Similar to above	Case manager
		
**6 months**		**Consultation with physician**	**Physician**
		
		Consultation with case manager Similar to above	Case manager
	
	**REGISTRY OF VARIABLES**		**Research team**

8 months		Consultation with case manager Similar to above	Case manager
		
**12 months**		**Consultation with physician**	**Physician**
		
		Consultation with case manager Similar to above	Case manager
	
	**REGISTRY OF VARIABLES**		**Research team**

The DMP will be supervised by the geriatricians on the research team, who will progressively delegate clinical functions to the case manager. A training programme for case managers will be conducted before the beginning of the trial. The DMP includes protocols for HF diagnosis and treatment will be implemented, based on the clinical guidelines of the European Society of Cardiology [14]. It also includes protocols to optimise the diagnosis and treatment of COPD, diabetes mellitus and depression. All cases of COPD are to be confirmed by spirometry, and patients and their caregivers will be trained on the use of inhaled drugs, smoking cessation, use of vaccines, and identification and management of exacerbations; in addition, treatment will be established in accordance with the Global Initiative for Chronic Obstructive Lung Disease (GOLD) recommendations. Patients with diabetes mellitus will receive an educational intervention on the symptoms of hypoglycaemia and hyperglycaemia, foot care, and, for patients treated with insulin, on the proper technique for its administration and self-monitoring of capillary blood glucose. In cases of depression, a clinical assessment of the diagnosis will be made if the score on the 15-item Yessavage test is > 5, and appropriate treatment will be initiated.

At outpatients clinic visits and telephone contacts, case managers will identify warning signs and symptoms of clinical deterioration from records of blood pressure and heart rate, changes in body weight, night-time cough, degree of dyspnea, decreased physical activity, and biomarkers such as renal function, natriuretic peptides and haemoglobin saturation by pulse oximetry.

For patients in the control group, the same intermediate and outcome variables will be recorded as in the intervention group, but the previously described educational activities and monitoring by the case manager will not be carried out. Follow-up will begin with the index admission and ends 12 months after discharge or in case of the patient's death.

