### Identification of participants, informed consent and randomisation

In each hospital a case manager with a degree in health sciences and special training in HF will identify and register cases admitted for HF each day by reviewing the diagnoses of those aged ≥ 75 years admitted in the acute care unit of the geriatric service. The case manager will then assess each patient and carry out the following activities:

i- Verify the study inclusion and exclusion criteria.

ii- Inform patients (verbally and in writing) and their caregivers (when considered necessary and with the patient's consent) of the characteristics of the DMP and confirm their agreement to participate by asking them to sign the informed consent document.

iii- Assign the patient to the intervention or control group. Randomisation will be conducted independently in each centre. Consecutively numbered envelopes, containing the group to which each patient should be assigned, will be used for this purpose. The envelope will be opened only at the time of patient assignment, to assure concealment of the randomisation list.

iv- Coordinate patient assessment, record the information in the case report form, and transcribe the information to a computerized database.

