Number of emergency department visits	^#^To be detected by review of the computerized clinical history or by the hospital admission records, counting all episodes after the date of discharge of the index admission. The number of these visits directly related with heart failure will be recorded.
Intermediate outcome variables	^#^Knowledge of disease ^#^Self-care measures
Final outcome variables	^#^Readmission.- all hospitalisation episodes of more than 24 hours following the date of discharge of the index admission. The following variables will be recorded: number and proportion of patients who are readmitted, number of readmissions per patient, and length of hospital stay during readmissions. ^#^Death.- To be determined by follow-up of each patient. This will be documented in the clinical history and the mortality registries. ^#^Quality of life.- Measured by the Minnesota Living With Heart Failure Questionnaire

ADLs: Basic activities of daily living; IADLs: Instrumental activities of daily living; * Variables to be registered only during the index admission; # Variables to be registered at the index admission and at 6 and 12 months.

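### As listed, the baseline interview, including the MLWHFQ, follows allocation and falls to the case manager who then delivers the DMP, so an allocation-related shift would pass straight into the quality-of-life change score

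*Protocol article*

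**What the plan says.** **Order of steps.** The shared admission entry of Table 1 starts with the eligibility review and continues "Informed consent Randomisation BASELINE VARIABLES", and the column for who does the work names the case manager. The section on identification of participants, informed consent and randomisation gives the case manager a numbered list of tasks. Item three is "iii- Assign the patient to the intervention or control group", with the explanation that "The envelope will be opened only at the time of patient assignment, to assure concealment of the randomisation list". Item four is "iv- Coordinate patient assessment, record the information in the case report form, and transcribe the information to a computerized database".

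**Who measures.** The section describing the intervention has the case manager carry out the programme. At 6 and 12 months, Table 1 assigns the recording of variables to the research team. The Study variables section says that information comes from interview with the patient or primary caregiver and from the clinical record.

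**What the baseline is used for.** Table 2 marks the MLWHFQ, disease knowledge, and knowledge of treatment and self-care with the symbol defined as "Variables to be registered at the index admission and at 6 and 12 months". The Statistical analysis section defines the quality-of-life effect as the between-group difference in the change in MLWHFQ score.

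**Knowledge and self-care.** In Table 1, the intervention column at admission contains, in the same cell as the educational session, "Questionnaires on self-care and disease knowledge for patient and caregiver". The control column has no such entry. The description of the intervention says that for controls "the same intermediate and outcome variables will be recorded as in the intervention group".

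**The concern.** Randomisation makes the groups comparable on what is measured before allocation is known. It gives no such protection to an interview held afterwards. If the case manager knows that a patient is about to enter the programme, the way questions are put or answers are scored may differ. A patient or caregiver who knows the assignment may also answer differently.

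The MLWHFQ is one of three final outcomes and the only one analysed as a change from baseline. A distorted baseline in one arm would look like a treatment effect, or would hide one. Neither intention-to-treat analysis nor a blinded follow-up interview would repair it.

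A second, smaller matter is that disease knowledge and self-care are intermediate outcomes tied to a secondary objective. Table 1 can be read as collecting these questionnaires at admission in one arm only, beside the teaching session, which conflicts with the rest of the article.

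**Working it through.** **1. Order of steps.** Two places bear on sequence.

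| Place | Order given |
|---|---|
| Table 1, admission entry | eligibility, consent, randomisation, baseline variables |
| Numbered task list | (i) eligibility, (ii) consent, (iii) assignment by envelope, (iv) assessment and case report form |

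They agree. The list is introduced by a clause saying that the case manager then assesses each patient and carries out the listed activities. That clause covers the whole list, whose first item is eligibility, so it does not place the baseline interview before item (iii). Nothing in the article says that baseline interviews precede the envelope or are held by someone unaware of allocation.

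**2. How a shift propagates.** Let B be the baseline score and F the follow-up score. The estimated effect is

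mean(F − B) in the intervention group − mean(F − B) in the control group.

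If allocation shifts the mean of B in the intervention group by b points relative to control, and nothing else differs, the estimate moves by −b. The documents give no basis for the sign or size of b.

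**3. Illustration of size.** The article gives no MLWHFQ standard deviation, so there is no stated figure to reproduce first.

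Inputs:
- n = 350 per group (Study size).
- Alpha = 5% (Study size), taken as two-sided (assumed).
- SD of change = 15 to 30 points (assumed).
- b = 1, 2 or 3 points (assumed).
- True effect = 0.

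Formulas, with Φ the standard normal distribution function:
- SE = SD × √(2/n), with √(2/350) = 0.0756.
- False-positive rate = Φ(b/SE − 1.96) + Φ(−b/SE − 1.96).

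For b = 2:
- SD 15: SE = 1.134, b/SE = 1.764, rate = Φ(−0.196) + Φ(−3.724) = 0.422.
- SD 30: SE = 2.268, b/SE = 0.882, rate = Φ(−1.078) + Φ(−2.842) = 0.143.

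| SD of change | SE | b = 1 | b = 2 | b = 3 |
|---|---|---|---|---|
| 15 | 1.134 | 14% | 42% | 75% |
| 20 | 1.512 | 10% | 26% | 51% |
| 25 | 1.890 | 8% | 19% | 36% |
| 30 | 2.268 | 7% | 14% | 26% |

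**4. Fewer patients analysed.** Deaths will reduce the number with 12-month scores. With 250 per arm (assumed), √(2/250) = 0.0894. For b = 2 the rate is then 32% at SD 15 (SE 1.342) and 12% at SD 30 (SE 2.683).

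**5. Knowledge and self-care.** Table 2 and the statement about controls call for these measures in both groups at the index admission. Table 1 names the questionnaires only in the intervention cell, although its shared baseline entry, which comes first, may already include them. The article does not say whether the intervention-column entry is that baseline or an additional check within the programme.

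**The case against.** **The timing is inferred.** No sentence says that the MLWHFQ interview follows the envelope. Order within one table cell is weak evidence, item four of the task list can be read as a general data-handling duty, and coordinating an assessment need not mean conducting it. A journal article also condenses the full protocol. This stands in part and lowers confidence. Still, two lists agree, nothing contradicts them, and Table 1 names the case manager.

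**Knowledge measured after teaching, or in one arm only.** A reader might infer this from the intervention-column entry. The documents do not support it. That entry is not called a baseline, the shared baseline entry comes before the educational session, and Table 2 marks these measures without restriction by group. What stands is an ambiguity to reconcile.

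**Every baseline comparison is at risk.** A reader might infer this too, but the Statistical analysis section names only one change score. Readmission and death are analysed as time to event and use no baseline score. Age, sex and laboratory values are hardly open to interviewer influence.

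**The size is hypothetical.** The SD, the shift and its direction all come from outside the article, and a shift of 2 or 3 points is small beside the 10 points that the article calls clinically relevant. This stands: the figures show sensitivity and are not a forecast. A shift too small to matter clinically can nevertheless raise the false-positive rate well above 5% at this sample size.

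**Conclusion.** The point holds in a limited form. As listed, the interview-based baseline is recorded after allocation is known, under the person who then delivers the programme, whereas another team records follow-up. This opens a route for bias into one of the three final outcomes, and the planned change-score analysis cannot close it.

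The article shows that bias could arise, not that it does. With an assumed SD of change of 15 to 30 points, 350 analysed per arm and no true effect, a 2-point differential shift would raise the false-positive rate from 5% to about 14% to 42%. With fewer patients analysed the rate would be lower.

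This should be fixed, but it does not undermine the trial as a whole. Confidence is moderate, because the order is taken from lists and not from an explicit statement.

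**What to change.** - Reorder the task list and the admission entry of Table 1 so that eligibility, consent and all baseline questionnaires, in both groups, are completed and recorded before the envelope is opened. If that is already the practice, one sentence and a corrected table settle the matter.
- Reconcile Table 1's intervention-only entry for self-care and knowledge questionnaires with the statement about controls and with the Table 2 footnote. Make clear that the baseline knowledge and self-care measures are taken in both groups before any teaching. If the intervention-column entry is a separate programme check, label it so.

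The cost is small, since the same tasks are done in a different order. A few patients may complete the baseline interview and then not be randomised.

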### Study variables

In addition to the inclusion and exclusion criteria, four types of variables will be collected: psychosocial, biomedical, treatment prescribed, and intermediate and final outcome variables (table 2). Episodes of hospital emergency care will also be recorded. The intermediate outcome variables are knowledge of the nature and management of HF and of comorbidity, and compliance with recommendations on lifestyle and drug treatment. The final outcome variables are health-related quality of life (assessed using the Minnesota Living with Heart Failure Questionnaire [MLWHFQ]), hospital readmissions, and total mortality. The outcome variables are measured at 6 and 12 months after the DMP begins. The information is collected through interview with the patient or primary caregiver and review of the clinical record.

**Table 2 T2:** Data collected in the study

Type of data	Variables
Definition of inclusion criteria	Hospitalisation.- hospital stay at least one night. Heart failure.- Framingham and European Society of Cardiology criteria Comorbidity.- Charlson index and other (see text) [34]
Psychosocial variables	*Sex ^#^Dependence in ADLs and IADLs.- Index of Katz [35] and Lawton [35,36] ^#^Quality of life.- Minnesota Living With Heart Failure Questionnaire [37] ^#^Depression.- 15-item Yessavage depression scale [38] ^#^Cognitive function.- Lobo cognitive miniexam [39] ^#^Health literacy.- SHALSA questionnaire[40] ^#^Knowledge of disease [33] ^#^Knowledge of treatment and self-care measures [41] *Housing conditions [42] *Social support.- OARS questionnaire [43] ^#^Treatment compliance.- interview and Morisky-Green test.
Biomedical variables	*Age *Pneumococcal and influenza vaccinations *Cardiovascular risk factors.- hypertension, smoking, diabetes, hypercholesterolemia and obesity. *Factors leading to admission *Length of hospital stay *Aetiology of heart failure ^#^Functional class (NYHA) *Ejection fraction.- transthoracic echocardiography ^#^Blood sodium, NTpBNP, creatinine and glucose ^#^Blood pressure, height and weight (body mass index)
Treatment	^#^Total number of drugs ^#^Drugs.- loop and potassium-sparing diuretics, angiotensin converting enzyme inhibitors, angiotensin receptor blockers, beta-blockers, antiplatelets, anticoagulants, statins ^#^Adverse effects associated with treatment
Number of emergency department visits	^#^To be detected by review of the computerized clinical history or by the hospital admission records, counting all episodes after the date of discharge of the index admission. The number of these visits directly related with heart failure will be recorded.
Intermediate outcome variables	^#^Knowledge of disease ^#^Self-care measures
Final outcome variables	^#^Readmission.- all hospitalisation episodes of more than 24 hours following the date of discharge of the index admission. The following variables will be recorded: number and proportion of patients who are readmitted, number of readmissions per patient, and length of hospital stay during readmissions. ^#^Death.- To be determined by follow-up of each patient. This will be documented in the clinical history and the mortality registries. ^#^Quality of life.- Measured by the Minnesota Living With Heart Failure Questionnaire

ADLs: Basic activities of daily living; IADLs: Instrumental activities of daily living; * Variables to be registered only during the index admission; # Variables to be registered at the index admission and at 6 and 12 months.

### Study size

In previous studies we observed that about 30% of HF patients are readmitted every 6 months [11]. These studies were conducted in hospitals and with patient's inclusion criteria different from those in the HF-Geriatrics, and within patients with less use of effective drug treatments than at present. Accordingly, under the conservative assumption that the annual frequency of readmission will be 40%, and that the frequency of readmission is similar in all study hospitals, 700 patients will need to be recruited (350 in each group) to detect, with an alpha error of 5% and a statistical power of 80%, a 20% reduction in hospital admission. This analysis assumes, as can be expected, that no patients will be lost to follow-up. A total of 700 patients also allows to detect, with an alpha error of 5% and 80% power, differences of 10 points (clinically relevant) in the MLWHFQ, assuming that patients in the control group have a mean score of 50 points on this questionnaire [11].

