### Management of HF

There is good evidence in patients with HF and high risk of hospitalisation that multidisciplinary strategies based on coordination and continuity of care can reduce mortality by 25%, hospital admissions for HF by 26-44%, and admissions for any cause by 19-27%, without increasing length of stay [17]. Thus, implementation of these disease management programmes (DMPs) is recommended in the major clinical practice guidelines [13,14]. In these DMPs a case manager provides patients and their caregivers with sufficient information and support to develop and comply with a plan to control HF. The case managers also reinforce compliance with treatment and detect early signs of HF decompensation.

In Spain, several DMPs have been evaluated in elderly HF patients. Morcillo et al. randomised 70 patients with severe HF and major systolic dysfunction (NYHA III or IV and left ventricular ejection fraction < 35%), previous hospitalisation for HF and mean age 79.1 years to "usual care" versus intervention by a case manager. At 6 months follow-up there were fewer deaths, emergency department visits and hospital readmissions in the intervention group [18]. However, the exclusion criteria were very strict, so that these patients may not be representative of many patients with HF. Atienza et al., in a randomised trial in 338 patients with a mean age of 68 years, showed that a DMP in tertiary hospitals can reduce readmissions for HF by 30% [19]. Lupón et al. obtained a 49% reduction in admission of patients with HF after 1 year of applying a HF programme (non-randomised before-and-after analysis) [20]. Brotons et al. recently reported a randomised home-based intervention study in 283 patients with a mean age of 76 years, 89% of whom had NYHA class III-IV HF. They observed a considerable reduction in the combined endpoint readmission or death at 1-year follow-up; however, only 25% of the patients initially evaluated could be included because the rest either did not meet the selection criteria or refused to participate [21].

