The main strengths of this study are random assignment to the intervention, concealment of the randomisation list, intention-to-treat analysis, and the very nature of the DMP designed. This DMP follows the recommendations of the major scientific societies in this field (13,14) and has been refined through a literature search for successful interventions. In addition, the intervention will be adapted to the educational level and visual limitations of most patients with the following measures: a) selection of a limited number of self-care skills to manage HF, COPD, diabetes mellitus and depression, to identify the warning signs of decompensation, and to comply with treatment [33]; b) implementation of only two brief educational sessions, the first during hospitalisation and the second on the day of discharge, as well as a telephone call 15 days after discharge; c) development of printed educational materials with brief text and large print, avoiding technical terms and with numerous explanatory pictures, to be given to patients in the intervention group on the day of hospital discharge; d) provision of a telephone contact number to patients so they can ask questions or resolve any issues they may have.

We plan to conduct specific training and certification of the case managers in the coordinating centre and to develop protocols for each of their activities. This ensures that the same intervention will be applied similarly in all participating centres and that, if the efficacy of the DMP is shown, it can easily be expanded to other health care settings.

The main challenges of the project are recruitment of study participants, avoidance of contamination of the intervention between the two trial groups, and minimization of losses to follow-up. To ensure sufficient recruitment, we have reviewed the basic hospital discharge dataset for each participating hospital, and have found that they each admit at least 100 patients with the characteristics needed for the project every 6 months. To avoid contamination, the case manager will conduct the DMP in a separate consultation, at a time of day other than when patients usually receive care. Finally, to minimize losses to follow-up, the intervention will be brief and will include only a small number of hospital visits. In addition, patient access to the case manager will be facilitated (by telephone or in person) so that any questions or problems that arise during the intervention can be addressed.

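### With 350 patients per group, power for a 20% reduction from 40% readmission is about 60%, not the stated 80%; that size fits a fall from 40% to 30%

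*Protocol article*

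**What the plan says.** The Study size section gives a complete calculation for readmission. It recalls that about 30% of patients were readmitted every 6 months in earlier studies, notes that those studies differed in hospitals, inclusion criteria and drug treatment, and then works "under the conservative assumption that the annual frequency of readmission will be 40" per cent. From this it derives 350 patients per group "to detect, with an alpha error of 5% and a statistical power of 80%, a 20% reduction in hospital admission". It does not say whether the reduction is relative or absolute, or whether the test is one- or two-sided.

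On losses it adds: "This analysis assumes, as can be expected, that no patients will be lost to follow-up". The Discussion, however, counts "minimization of losses to follow-up" among the main challenges of the project.

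For the effect to be expected, the Background (Management of HF) reports that multidisciplinary programmes reduce "admissions for any cause by 19-27" per cent.

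**The concern.** All the inputs to the sample size are stated, so the result should be reproducible, and it is not. A 20% relative reduction from 40% is a difference of 8 percentage points, which is small for 350 per group. A 20-point difference is so large that 350 would be far too many. The stated size lies between the two readings and matches neither.

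Readmission is the only event outcome for which the article states a power; the other power statement concerns the quality-of-life score. If the true power is well below 80%, a real benefit of the size cited in the Background could easily give a non-significant result. A reader relying on the stated 80% would then take that result as stronger evidence against the programme in elderly patients than it is.

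**Working it through.** **Inputs, all from Study size:** control proportion p1 = 0.40; a reduction of 20%; alpha 5%; power 80%; 350 per group, 1:1; no losses. Sidedness is not stated, so two-sided is taken first (z = 1.960 and 0.8416; squared sum 7.849).

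**1. The plan's figure, relative reading: p2 = 0.80 × 0.40 = 0.32.**

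Unpooled variance:

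n = 7.849 × (0.40×0.60 + 0.32×0.68) / 0.08² = 7.849 × 0.4576 / 0.0064 = 561.2, so 562 per group.

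Pooled variance under the null (mean proportion 0.36): 564 per group. With continuity correction: 589.

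**2. Power at 350 per group for 40% vs 32%.**

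z = [0.08×√350 − 1.960×√(2×0.36×0.64)] / √0.4576 = (1.4967 − 1.3305) / 0.6765 = 0.246, so power = 59.7%.

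The arcsine method gives 59.8%, and exact enumeration of the chi-square test 60.0%.

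**3. Other readings of the same inputs.**

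| Reading | Needed per group for 80% | Power at 350 per group |
|---|---|---|
| 40% vs 32%, two-sided | 564 | 59.7% |
| 40% vs 32%, one-sided 5% | 445 | 71.3% |
| 40% vs 20% (absolute) | 82 (79 unpooled) | about 100% |
| Poisson rates 0.40 vs 0.32, two-sided | 883 | below 80% |

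None gives 350 per group at 80%.

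**4. Time-to-event version**, since the Statistical analysis section plans Cox regression. Under proportional hazards, 40% vs 32% is a hazard ratio of ln(0.68)/ln(0.60) = 0.755. Schoenfeld's formula needs 4×7.849/(ln 0.755)² ≈ 398 events; 350 × (0.40 + 0.32) = 252 are expected, giving 60.7% power. Were the 20% instead meant as a hazard ratio of 0.80, 631 events would be needed against about 257 expected, with power 43%.

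**5. What 350 per group does fit at a 40% control rate.** For 40% vs 30%: unpooled 7.849 × (0.24 + 0.21) / 0.01 = 353.2, so 354; pooled 356. Power at 350 is [0.10×√350 − 1.960×√(2×0.35×0.65)] / √0.45 = (1.8708 − 1.3221) / 0.6708 = 0.818, so 79.3% (exact 79.6%). The smallest reduction detectable with 80% power is from 40% to 29.9%, or 25.2% relative.

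**6. Power across the cited effect range, 350 per group, two-sided.** A 19% reduction (40% to 32.4%): 55%. A 20% reduction: 60%. A 27% reduction (40% to 29.2%): 85%.

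**7. Losses.** The article gives no loss rate, so 5% and 10% are assumptions. With 10% loss, 315 per group remain: power is 55% for 40% vs 32% and 75% for 40% vs 30%. With 5% loss (332.5 per group on average): 57.5% and 77%.

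**The case against.** The strongest reply is that the slip may lie in the 40% and not in the 20%. The section itself reports about 30% readmitted every 6 months, which at a constant rate is 1 − 0.70² = 51% a year. A 20% relative reduction from 51% has 77% power at 350 per group, and from 53% about 80%. The Kaplan-Meier analysis also counts readmission or death, whose frequency cannot be lower than that of readmission alone. Since 40% is called conservative, actual power could exceed 60%.

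This stands in part. That a 25% reduction was intended is inferred from the arithmetic; the article nowhere says so. The 60% is also conditional on a 40% control rate. But the section considers the 6-monthly figure and deliberately replaces it with 40%, and it gives no rate for the composite. The stated 80% therefore does not follow from the stated inputs, and even 51% falls slightly short.

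Two smaller objections are fair. Nothing in the section equates the 20% with a hazard ratio of 0.80, so the 43% applies only under that reading and the conclusion does not depend on it. On losses, patients who cannot be followed up are excluded, and readmission and death are taken from records and registries, so low loss is plausible for these outcomes. The zero-loss assumption is openly stated; its tension with the Discussion is a secondary point, and the arithmetic fails with no losses at all.

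**Conclusion.** The stated power is wrong as written. At 40% control readmission, a two-sided 5% test and no losses, 350 per group give about 60% power for a 20% relative reduction, some 20 percentage points below the claim. Reaching 80% would take about 564 per group, or 1,128 in all. Neither a one-sided test nor an absolute reading reconciles the figures. At the stated control rate, the design has about 80% power for a fall from 40% to 30%, a 25% relative reduction. For true reductions of 19-20%, the lower end of the range the article cites, the chance of missing the effect is 40-45%. These figures would improve with a higher event rate and worsen with losses. This must be corrected, because it misstates what the trial can detect on a main outcome.

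**What to change.** Keep 700 patients and rewrite the readmission part of Study size. Suggested content: with 40% annual readmission in the control group and a two-sided 5% test, 350 patients per group give about 80% power (79%) for a 25% relative reduction, from 40% to 30%, and about 60% for a 20% relative reduction, from 40% to 32%. State explicitly that the reduction is relative and the test two-sided. If the calculation was in fact made with a higher control rate, state that rate and its justification instead.

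Remove the remark that zero loss is to be expected, and give the power at assumed losses: at 5% about 77% (40% vs 30%) and 57% (40% vs 32%); at 10% about 75% and 55%.

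The cost is one rewritten paragraph and a less favourable stated detectable effect. Patient numbers, design and analysis do not change.
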